#### **Definition of Prevention and Improvement (CTCAE v5.0):**

- *Prevention*: Absence of oral mucositis throughout evaluation period (“none → none”).
- *Improvement*: Baseline Grade 1/2/3 → lower grade or “none” after evaluation.
- Absence of mucositis is defined per Secondary Endpoint 4 (overall oral mucosal status).

#### **For Oral Pain (CTCAE v5.0):**

- *Prevention*: “Grade 0 → Grade 0”.
- *Improvement*: Baseline Grade 1/2/3 → lower grade or “Grade 0”.

### **4) Safety Evaluation**

#### **Safety Endpoints:**

1. Adverse events and illnesses.
2. Device malfunctions.
3. Laboratory tests.

#### **Methods:**

- Adverse events, illnesses, and device malfunctions will be summarized by participant and by event.
- Adverse events and illnesses will be coded using MedDRA/J, and device malfunctions using the Japanese Medical Device Failure Terminology.

- Events will be tabulated by System Organ Class (SOC) and Preferred Term (PT), and summarized by causal relationship and severity when appropriate.
- For laboratory tests, summary statistics (as in Section 2.1) will be calculated by group.

## **5) Significance Level and Confidence Coefficient**

- Significance level: 5% (two-sided)
- Confidence coefficient: 95% (two-sided)

## **9. Study Period**

From the date of publication on the Japan Registry of Clinical Trials (jRCT) following approval by the Certified Review Board until December 31, 2027.

Registration deadline: February 28, 2027.

*jRCT (Japan Registry of Clinical Trials):*

<https://jrct.mhlw.go.jp/>

## **10. Criteria for Participant Selection**

### **(1) Inclusion Criteria**

Participants must be able to understand the study and provide written informed consent, and must meet all of the following criteria:

1. Patients with breast cancer scheduled to receive chemotherapy (including molecular-targeted agents or immune checkpoint inhibitors) at a participating institution.
2. No clinical signs of oral candidiasis.
3. Presence of tooth–mucosa contact.
4. Age  $\geq 18$  years at the time of consent.
5. ECOG Performance Status 0–1.
6. Oral feeding is functionally possible.

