| Approval                   | /                                                                                                                                                                                                                                                                                                                                                                                                          |
| Certification No.          | 30500BZX00107000                                                                                                                                                                                                                                                                                                                                                                                           |
| Intended use               | To cover defective or sharp tooth surfaces for short periods to protect oral mucosa and, through gradual release of cetylpyridinium chloride (CPC), to suppress biofilm formation and prevent infection. The device also reduces mechanical irritation to the oral mucosa caused by carious lesions or sharp edges due to attrition. CPC has been shown to inhibit Streptococcus mutans growth in a |

| Item                      | Description                                                                                                                                                                                                                                                                                                                                                                                                                                                                                                                            |
|---------------------------|----------------------------------------------------------------------------------------------------------------------------------------------------------------------------------------------------------------------------------------------------------------------------------------------------------------------------------------------------------------------------------------------------------------------------------------------------------------------------------------------------------------------------------------|

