|                           | concentration-dependent manner, thereby reducing biofilm formation on the cured surface.                                                                                                                                                                                                                                                                                                                                                                                                                                               |
| Mode of use        | Clean the tooth surface. Remove one single-use blister pack just before use. Using gloved fingers (preferably nitrile gloves that are easy to shape and non-sticky), directly apply the paste to the causative tooth. Remove excess material, ask the participant to occlude, adjust the shape, and initiate polymerization by light irradiation. If dislodgment is expected, bonding treatment should be applied before filling. Remove with an excavator or explorer if necessary. The device can remain in place for up to 30 days. |
| Properties         | / Light-curable paste composed of urethane dimethacrylate, polymer, silica, photoinitiator, and cetylpyridinium chloride.                                                                                                                                                                                                                                                                                                                                                                                                              |
| Specifications     |                                                                                                                                                                                                                                                                                                                                                                                                                                                                                                                                        |

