### 1) Comparative Period – Intervention Group

(Standard care [oral care, Episil® oral liquid, etc.] + investigational device)

- Record the start date of the comparative period.

- 226 • In addition to conventional oral care and protectants, the investigational device is applied to
- 227 teeth responsible for mucosal trauma (e.g., crowding, sharp edges due to fracture or attrition).
- 228 • If multiple candidate teeth exist, all will be filled and individually assessed.
- 229 • For procedural consistency, filling will be performed by the site investigator or co-
- 230 investigator (dentist).
- 231 • The light-curing and bonding process follows the method described above.
- 232 • The device remains in place throughout the 14–28-day period.
- 233 • If chemotherapy is postponed, the device will be removed and reapplied in coordination with
- 234 the rescheduled chemotherapy.
- 235 • After final evaluation (Day 14, 21, or 28), the device will be removed.
- 236 • If dislodged earlier, the date and time will be recorded.
- 237 • If continued application is deemed inappropriate or the participant wishes to discontinue, the
- 238 device will be removed and final assessments performed (see Section 14.5 Discontinuation
- 239 Criteria)

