### Note on Evaluations:

For the evaluation items “*Oral mucositis (CTCAE v3.0 subcriteria)*” and “*Pain NRS at the affected site*”, the efficacy of the investigational device is principally limited to the *designated affected site*—defined in inclusion criterion (3) as “a site where contact occurs between teeth and oral mucosa” (corresponding to the filled site in the intervention group).

Therefore, this site must be identified in advance on Day 1 for all participants, including the control group (which does not receive device filling).

If multiple affected sites are present, each must be assessed individually.

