### **(2) Exclusion Criteria**

Participants meeting any of the following criteria will be excluded:

1. Receiving, previously received, or scheduled to receive radiotherapy to the head and neck region.
2. Having fewer than 10 remaining teeth.
3. Currently wearing dentures.
4. Known allergy to cetylpyridinium chloride (CPC) or resin materials.
5. Pregnant or possibly pregnant.
6. Using or planning to use medical narcotics, opioids, or oral steroid ointments (dexamethasone).
7. Scheduled to undergo dental treatment during the study period.
8. Unable or unwilling to complete self-assessment questionnaires under physician guidance.
9. Any other condition judged by the investigator to make the participant unsuitable due to clinical, social, or conflict-of-interest–related reasons.

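### Eligibility and the target site require only tooth–mucosa contact, but the device is for causative or sharp teeth, so an eligible patient may have no tooth to fill

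*Protocol*

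**What the plan says.** The protocol describes the tooth of interest in two ways.

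**By contact.**
- Section 10(1), inclusion criterion 3, reads in full "Presence of tooth–mucosa contact". No other inclusion or exclusion criterion mentions sharpness, crowding, fracture or trauma.
- The Note on Evaluations in Section 6 refers back to criterion 3 and defines the designated affected site as "a site where contact occurs between teeth and oral mucosa".

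**By cause or defect.**
- The intended use in Section 4(4)① is "To cover defective or sharp tooth surfaces for short periods to protect oral mucosa".
- The mode of use in the same table tells the operator to "directly apply the paste to the causative tooth".
- The intervention procedure in Section 4(4)② applies the device to "teeth responsible for mucosal trauma (e.g., crowding, sharp edges due to fracture or attrition".

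**The link between the two.** The Section 6 note says that the contact site is the one "corresponding to the filled site in the intervention group", and that "this site must be identified in advance on Day 1 for all participants, including the control group". The primary endpoint (Section 8(2), part 2) is scored at this target site, and a site free of mucositis before and after counts as a success. The FAS in Section 8(1) is limited to randomised participants who were treated and have at least one efficacy assessment.

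**The concern.** Contact and trauma are different conditions. A tooth can touch cheek, lip or tongue without injuring it. A patient with contact only meets criterion 3, is registered and is randomised, yet the intervention procedure names no tooth to fill, and the protocol does not say what happens next. There are two ways out, and each breaks a stated rule:

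- **No tooth is filled.** The target site then has no filled counterpart, contrary to the Section 6 note. It is also unclear whether the patient counts as treated for the FAS. If such patients are dropped, only the intervention arm loses them, because their control counterparts cannot be told apart.
- **A contact tooth is filled anyway.** The device is then used outside the teeth described in Section 4(4).

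Either way, the primary endpoint is scored at a site that may not be the kind of site the device is meant for. Four institutions may also read criterion 3 differently and admit different populations. If unfilled patients stay in the analysis, they pull the two success rates together.

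**Working it through.** **Step 1: reproduce the planned size.** Section 7 gives 50% v 25%, two-sided 5%, 90% power, Pearson chi-square, 77 per group. With pooled variance under the null and no continuity correction:

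n = [(1.960·√(2p̄(1−p̄)) + 1.2816·√(p₁(1−p₁)+p₂(1−p₂))) / (p₁−p₂)]²

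Here p̄ = 0.375, the first root is 0.6847 and the second is 0.6614. So n = [(1.3419 + 0.8477)/0.25]² = 76.7, which rounds up to 77. The stated figure is correct.

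Power at 77 = Φ[((p₁−p₂)√77 − 1.960·0.6847)/0.6614] = Φ[(2.1937 − 1.3419)/0.6614] = Φ(1.288) = 90.1%.

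**Step 2: compare the passages.** Take an eligible patient with a contact tooth that causes no trauma.

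| Place | Result for this patient |
|---|---|
| Section 10(1), criterion 3 | Meets it |
| Section 6 note | Has a target site, said to be the filled site |
| Section 4(4)①, intended use and mode of use | No defective, sharp or causative tooth |
| Section 4(4)②, intervention procedure | No tooth to fill |

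The second row cannot hold together with the last two.

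**Step 3: a scenario for the unfilled branch.** Three inputs are assumptions, not protocol figures:
- a share f of patients has no tooth to fill;
- these patients succeed at rate q in both arms (no device effect);
- 50% v 25% holds in the rest.

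Then p₁ = 0.50(1−f) + fq and p₂ = 0.25(1−f) + fq, so the difference is 0.25(1−f) whatever q is. I took q from 25% (the planned control rate) to 80% (most such sites stay free of mucositis and count as successes).

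Example, f = 20% and q = 25%: 0.45 v 0.25, p̄ = 0.35, roots 0.6745 and 0.6595. Power = Φ[(0.20·8.775 − 1.960·0.6745)/0.6595] = Φ(0.656) = 74.4%.

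| f | Power, q = 25% | q = 60% | q = 80% | n per arm for 90% power (range over q) |
|---|---|---|---|---|
| 0 | 90.1% | 90.1% | 90.1% | 77 |
| 10% | 83.4% | 82.1% | 81.5% | 94–99 |
| 20% | 74.4% | 71.4% | 70.6% | 118–129 |
| 30% | 63.4% | 59.1% | 58.5% | 152–170 |

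**Step 4: exclude without replacing.** If the same patients were screened out and never replaced, 77(1−f) per arm would remain at 50% v 25%. That is 69.3, 61.6 and 53.9 per arm for f = 10%, 20% and 30%, with power 86.8%, 82.6% and 77.2%. Each figure is above the diluted value in the same row.

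**The case against.** A reader might infer more than the protocol supports. Because exclusion 2 removes anyone "Having fewer than 10 remaining teeth", it is tempting to say that practically every remaining patient has tooth–mucosa contact, that criterion 3 screens out nobody, and that patients with nothing to treat are therefore being randomised. The protocol gives no prevalence of contact and no share of patients without a causative tooth. That step is general dental reasoning.

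Other points on the sponsor's side:

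- **The Section 6 note can be read the other way.** By equating the criterion 3 site with the filled site, it may intend every eligible patient to have a fillable tooth. The trauma wording in Section 4(4)② is illustrated by examples only, and these include crowding, which need not involve a sharp edge. This is a fair reading, but it needs contact to mean the same as trauma, and Section 4(4) does not say so.
- **Exclusion 9 allows an investigator to exclude an unsuitable patient.** That stands, but it is discretionary and does not mention this case.
- **Zero effect is not certain.** Section 4(4)① gives the device a second action, release of CPC against biofilm. If a smooth contact tooth is filled, some effect is possible. The scenario therefore applies only to unfilled patients.
- **The 50% and 25% may already describe the whole population.** Section 7 sets them as expected rates for this trial and lowers them from the exploratory 58.3% v 0.0% for stated uncertainties. Patients without a fillable tooth are not among the reasons given, but nor does Section 7 restrict the rates to a subset.
- **Accrual.** At the minimum of 10 participants per year per site, four sites need 154/40 = 3.85 years, and registration closes on 28 February 2027. A narrower criterion could slow this. Step 4 shows that this does not defeat the point: in the scenario, screening such patients out without replacement costs less power than admitting them.

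**Conclusion.** The inconsistency is in the text and holds without any assumption. Criterion 3 and the target-site definition rest on contact, Section 4(4) rests on a causative, defective or sharp tooth, and the Section 6 note treats the two as the same. Followed literally, an eligible intervention patient can have no tooth to fill, no filled target site and an unclear place in the FAS.

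The effect on power is conditional. It rests on an unstated share f, no device effect in unfilled patients, and 50% v 25% in the others. The loss from 90.1% is about 7 to 9 percentage points at f = 10%, 16 to 20 at 20% and 27 to 32 at 30%. If investigators already read criterion 3 narrowly, f is zero and nothing is lost. The protocol does not show that the trial is underpowered, and that should not be claimed.

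**What to change.** Reconcile criterion 3 in Section 10(1) and the Note on Evaluations in Section 6 with the intended use, mode of use and intervention procedure in Section 4(4), so that eligibility, target site and filled site share one definition. Which definition to adopt is for the sponsor to decide.

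Require the qualifying tooth or teeth and the corresponding mucosal site to be entered in the EDC at the screening oral examination, before full registration and randomisation, in both arms. At present the site is to be identified on Day 1, whereas the schedule places randomisation in the screening period. In an open-label trial, a loose definition then leaves room for the choice of site to differ by arm. Earlier recording alone would not settle who is eligible, so both changes are needed. State also whether an intervention patient in whom no tooth was filled counts as treated for the FAS.

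The cost is a wording amendment, one EDC field and a dental judgement at screening, where oral findings and intraoral photographs are already collected. Section 4(4)② requires a dentist only for the filling, so the screening examination may need one too. Some screen failures and slower accrual are possible.

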### **(2) Exclusion Criteria**

Participants meeting any of the following criteria will be excluded:

1. Receiving, previously received, or scheduled to receive radiotherapy to the head and neck region.
2. Having fewer than 10 remaining teeth.
3. Currently wearing dentures.
4. Known allergy to cetylpyridinium chloride (CPC) or resin materials.
5. Pregnant or possibly pregnant.
6. Using or planning to use medical narcotics, opioids, or oral steroid ointments (dexamethasone).
7. Scheduled to undergo dental treatment during the study period.
8. Unable or unwilling to complete self-assessment questionnaires under physician guidance.
9. Any other condition judged by the investigator to make the participant unsuitable due to clinical, social, or conflict-of-interest–related reasons.

## **11. Study Background and Scientific Rationale**

This is a multicenter, prospective, open-label, stratified, randomized, parallel-group confirmatory study designed to evaluate the preventive and pain-relieving efficacy of the investigational oral mucosal protectant.

The target sample size was determined to ensure both scientific validity and feasibility within the planned study duration.

## **12. Procedures for Obtaining Informed Consent**

The principal or sub-investigator will provide potential participants with the IRB-approved consent form and written information sheet, and will explain the study in full both verbally and in writing before obtaining written voluntary consent.

If new safety or efficacy information arises, or if protocol amendments could influence the participant's willingness to continue, updated information will be promptly provided. Revised consent and information documents will be submitted for Certified Review Board (CRB) approval prior to re-consent.

**The consent document must include the following information:**

1. Title of the specified clinical study, institutional approval, and notification to the Minister of Health, Labour and Welfare (MHLW).

2. Name of the medical institution and name/title of the principal investigator.
3. Reason for participant selection.
4. Expected benefits and risks of study participation.
5. Statement that participation is voluntary.
6. Explanation regarding withdrawal of consent.
7. Assurance that refusal or withdrawal will not result in disadvantageous treatment.
8. Procedures for public disclosure of study information.
9. Participant's right to access or review study-related materials and how to do so.
10. Protection of personal information.
11. Methods for storage and disposal of specimens and data.
12. Any sponsorship or involvement of manufacturers or other entities.
13. Procedures for handling inquiries and complaints.
14. Information on study-related costs.
15. Availability and comparison of alternative treatments.
16. Compensation and medical care in the event of health injury.
17. Details of Certified Review Board review and oversight.
18. Any other necessary items concerning the conduct of the study.

### **13. Handling of Personal Information**

All study personnel will comply with the Declaration of Helsinki and the Clinical Trials Act (Japan).  
Each participant will be assigned a unique study identification code.  
A linkage file between personal identifiers and study codes will be created and securely password-protected.  
Names and direct identifiers will be removed from all source data used for analysis.  
This linkage file will be securely stored throughout the study to prevent leakage.  
Publications and reports will not include any personally identifiable information such as names or birthdates  
Data obtained in this study will not be used for any purpose other than those specified in the protocol.

## **14. Anticipated Burden, Risks, and Benefits**

### **(1) Expected Benefits**

Participation may provide potential benefit by preventing or alleviating oral mucositis-related pain associated with chemotherapy through the use of the investigational oral mucosal protectant. After study completion, participants will continue to receive the most appropriate medical care as determined by the investigator, including consideration of study findings.

### **(2) Anticipated Risks and Disadvantages**

Participation may involve increased clinical visit time and additional effort for patient-reported evaluations.

There is a possibility of experiencing diseases or device-related events as described in Section 25(7) “Predictable Events,” which may require medical treatment such as outpatient or inpatient care.

Unexpected adverse events, permanent impairment, or even death cannot be completely ruled out.

Use of the investigational device provided by the sponsor will incur no cost to the participant.

In the event of serious health injury (death, or grade 1–3 permanent disability) directly attributable to study participation, compensation will be provided as described in Section 26, “Compensation for Health Injury.”

### **(3) Management of Adverse Events**

If an adverse event occurs, the investigator will immediately provide appropriate medical care, document the event in the medical record and eCRF, and inform the participant of the management plan.

If the investigational treatment is discontinued due to an adverse event, the participant will be promptly notified and managed appropriately.

### **(4) Protocol Amendments**

Safety-related information will be continuously reviewed, and the protocol and consent documents will be amended if necessary.

All amendments must be approved in advance by the Certified Review Board (CRB).

Amendments will be submitted to MHLW as follows:

739       • **Substantial amendment:**

- 740           1. *Notification of change in implementation plan* (Form No. 2, Ministerial Ordinance)  
741           2. *Revised implementation plan*

742       • **Minor amendment:**

- 743           1. *Notification of minor change in implementation plan* (Form No. 3)  
744           2. *Revised implementation plan*

745 For minor administrative changes (e.g., investigator contact details, institutional name updates),  
746 notification to the CRB will be made within 10 days, accompanied by submission of Form No. 3 to  
747 MHLW.  
748

749 **(5) Criteria for Discontinuation**

750 When continuation is deemed impossible, the investigator shall discontinue the participant's  
751 involvement, explain the reason if appropriate, and ensure that post-discontinuation medical care is  
752 provided without disadvantage.

753 **Reasons for discontinuation include:**

- 754       1. Participant requests to withdraw. (The reason will be confirmed if possible, but not required.)  
755       2. Worsening of primary disease, chemotherapy-related symptoms, or requirement for  
756       disallowed concomitant therapy.  
757       3. Occurrence of adverse events making continuation difficult.  
758       4. Noncompliance with the protocol.  
759       5. Ineligibility determined upon further observation after registration.  
760       6. Any other reason judged by the investigator to make continuation inappropriate.

761 **In case of treatment discontinuation:**

762 If continuation of the investigational treatment is deemed impossible for the above reasons, treatment  
763 will be discontinued with an appropriate explanation to the participant.

764 Participants who have received the investigational device will continue safety follow-up observations  
765 even after discontinuation.  
766

767 **15. Storage and Disposal of Study Records and Data (Including Retention Period)**

768 The principal investigator shall prepare and maintain records regarding:

- 769       1. Identification of each study participant.

2. Clinical care and testing performed for participants.
3. Details related to study participation.
4. Any other records necessary for the conduct of this study.

In this study, each participating institution will provide data to Okayama University Hospital, where the coordinating investigator is based. All data exchanges will be conducted so as to exclude personally identifiable information.

Each institution will manage personal information in accordance with its internal policies.

All collected data will be securely stored in a locked facility (for Okayama University Hospital: the Department of Periodontology, Graduate School of Medicine, Dentistry and Pharmaceutical Sciences) until five years after study completion, and will then be destroyed with appropriate safeguards for privacy.

Personal identifiers such as names, addresses, and dates of birth will be removed before storage.

Essential documents — including the study protocol, implementation plan, informed consent forms, summary report, correspondence with the Certified Review Board (CRB), monitoring documentation, participant code lists, CRFs, and any materials ensuring data reliability (as well as descriptions of the investigational device) — will be securely stored for the same period (five years post-study completion) and subsequently disposed of appropriately.

Electronic data will be permanently deleted, and paper records will be shredded.

